### Secondary endpoints

The follow-up of the clotting during the first heparin-free dialysis treatment will be performed at each hour throughout the dialysis session; clotting in the air traps will be assessed using the same semi-quantitative scale as described above.

The evaluation of the success rate during the second and the third consecutive heparin-free dialysis treatments will be as for the first heparin-free dialysis treatment. Treatments will be considered successful when there is: no complete occlusion of air traps or dialyzer rendering dialysis impossible (grade 4); no additional saline flushes to prevent clotting; no change of dialyzer or blood lines because of clotting; and no premature stoppage (early rinse-back) because of clotting. This evaluation will be performed by two independent observers as described in the aforementioned primary endpoint section.

Follow-up of the clotting during the second and the third consecutive heparin-free dialysis treatment will be performed at every hour; clotting in the air traps will be assessed using the same semi-quantitative scale as described above.

To undertake hemodialysis session efficacy assessment, the ultrafiltration (UF) achieved, weight loss, serum creatinine and urea reduction rates, as well as electrolytes changes will be documented during all dialysis sessions. To measure ease of use, the frequency and remaining volume of saline flushes will be documented. The occurrence of adverse events and serious adverse events during the study will be collected.

### Ethics

Inclusion in the study was initiated in 2011 after approval of the appropriate ethics committee (Comité de Protection des Personnes, Sud Est III Lyon, France; Comité Ético de Investigación Clínica, Vall d’Hebron Hospital, Barcelona, Spain; Comité Ético de Investigación Clínica, Germans Trias i Pujol Hospital, Barcelona, Spain; National Research Ethics Service, Yorkshire and the Humber – Sheffield, UK; Comité d’éthique, Université Libre de Bruxelles, Hôpital Erasme, Brussels, Belgium; Comité d’éthique de la recherche Centre hospitalier universitaire, Dr-Georges-L-Dumont, Moncton, Canada; Medisch Ethische Toetsingsingscommissie, Universitair Medisch Centrum Groningen, Groningen, the Netherlands; and the Independent Bioethic Committee for Scientific Research, Gdańsk Medical University, Gdańsk, Poland) and competent authorities where applicable. The study protocol was recorded prior to any enrolment at ClinicalTrials.gov: NCT01318486.

### Statistics

Allocation of treatments will be performed using a centralized, on-line randomization system. Patients will be assigned to treatment groups using block randomization stratified on centers.

### Justification of sample size

The main criterion of efficacy is the success rate in the Evodial group (test) compared to standard care (on-line predilution or saline flushes). After completion of the study, the analysis will follow a two-step procedure and the probability that the efficiency of Evodial is inferior to that of the standard care will be tested first. If that probability is rejected at the 5% significance level, that is if non-inferiority is demonstrated, then superiority will be tested. The probability of simultaneously falsely accepting inferiority and superiority being mutually exclusive, no adjustment of alpha error rate will be requested. According to the results, the conclusion will be: Evodial is inferior, not inferior but not superior, or superior to the standard care.

According to the data published on heparin-free treatment (with saline flushes or on-line predilution), the success rate of hemodialysis ranges from 65% to 85%. Recent works presented at the French Society of Nephrology, September 2010, meeting in Brussels, showed a 15% to 20% improvement of these success rates using preheparinated dialysis membranes (HeprAN, Gambro, or AN69 ST) [27,28]. The non-inferiority as well as superiority margins will be set to the same value of 15%. In the hypothesis of a 65% success rate (the most patient-consuming) in the control arm, a sample size of 126 patients per arm (252 for the entire sample) will provide the trial with 80% power to first conclude to non-inferiority then to superiority, with a one-tailed 5% error rate. Assuming an equal inclusion rate in all centers, 26 patients will be enrolled in each of the 10 centers, with 13 patients in each arm. Withdrawn patients will be replaced only if the patient has been randomized and no dialysis treatment could have been performed.

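### A lower limit at or below −15% would be reported as Evodial being inferior, although it shows only that non-inferiority was not demonstrated

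*Protocol article*

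**What the plan says.** All references are to the protocol article.

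- **Justification of sample size** sets a two-step procedure. Step 1 takes inferiority of Evodial as the hypothesis to be rejected: "If that probability is rejected at the 5% significance level, that is if non-inferiority is demonstrated, then superiority will be tested".
- The same section then lists the possible conclusions: "According to the results, the conclusion will be: Evodial is inferior, not inferior but not superior, or superior to the standard care". There is no fourth outcome.
- **Efficacy analysis, Primary objective** gives the decision rule. A one-tailed 95% interval for test minus reference is built by the Wilson method. Non-inferiority is accepted if its lower boundary is above −15%, then superiority if it is above +15%. No upper limit is used.
- The design values are in the sample-size section: "In the hypothesis of a 65% success rate (the most patient-consuming) in the control arm", 126 patients per arm, 80% power, "with a one-tailed 5% error rate", and a margin of 15 percentage points for both steps. The published control success rates are said to run from 65% to 85%.

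**The concern.** Three labels are listed, but only two have a criterion. A lower limit above −15% leads to *not inferior but not superior*, or to *superior* if it is also above +15%. Whatever remains can only be *inferior*. A wide interval around a difference near zero would then be reported in the same words as a convincing demonstration of harm to effectiveness.

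The one-sided 5% level limits false claims of non-inferiority. It does not limit false claims of inferiority; under this rule their frequency for an equally good device is the type II error. At stake is the wording of the primary conclusion of a 252-patient trial that the authors expect to influence care. Clinicians could be turned away from a device on inconclusive data.

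**Working it through.** **Inputs.** From Justification of sample size: 65% control success, margin 0.15, one-sided alpha 0.05, power 80%, 126 per arm. From Primary objective: the lower limit is compared with −15% and +15%, using the Wilson method.

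**Assumptions.** The article does not state the true difference behind the sample size; I take 0 (65% vs 65%). I read the Wilson method for a difference as the Newcombe interval built from the Wilson limits of each arm.

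**1. The plan's own figure.**
n = (z₀.₉₅ + z₀.₈₀)² × 2p(1 − p) / margin²
= (1.645 + 0.842)² × 2 × 0.65 × 0.35 / 0.15² = 125.03, rounded up to **126 per arm**.
This matches and supports the assumed difference of 0. A one-sided 2.5% level would give 159.

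Power at n = 126: SE = √(2 × 0.65 × 0.35 / 126) = 0.0601. Then Φ(0.15/0.0601 − 1.645) = Φ(0.851) = 80.3%. The chance of missing non-inferiority with an equal device is therefore 19.7% by normal approximation.

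**2. One data set.** Evodial 75/126 (59.5%), control 82/126 (65.1%), difference −5.6 points. Wilson limits with z = 1.645 are 0.5220 to 0.6644 for Evodial and 0.5784 to 0.7168 for control.
- Lower limit = −0.0556 − √[(0.5952 − 0.5220)² + (0.7168 − 0.6508)²] = −0.154
- Upper limit = −0.0556 + √[(0.6644 − 0.5952)² + (0.6508 − 0.5784)²] = +0.045

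The limits of −15.4% and +4.5% are compatible with Evodial being slightly better, yet the only label available is *inferior*.

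**3. How often this happens.** Exact enumeration over two independent binomials of size 126, with one-sided 95% limits and equal true rates:

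| True success, both arms | Lower limit ≤ −15% | of which upper limit ≥ 0 |
|---|---|---|
| 65% | 19.2% | 14.2% |
| 75% | 13.0% | 8.0% |
| 80% | 8.9% | 3.9% |
| 85% | 4.7% | 0.5% |

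At 65%, 14.2/19.2 = 74% of the *inferior* verdicts would rest on data that do not show Evodial to be worse. Using a two-sided 95% interval, the 14.2 points become 16.7.

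**4. Evodial truly better, control at 65%.** The lower limit is at or below −15% in 3.9% of trials at 70% vs 65%, 0.3% at 75% vs 65%, and less than 0.01% at 80% vs 65%.

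**5. With an upper-limit condition.** If *inferior* also required the upper one-sided 95% limit to be below 0, an equal device would get that label in 19.2 − 14.2 = 5.0% of trials at 65%, and in 4.7 − 0.5 = 4.2% at 85%.

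**The case against.** **The operative rule assigns no verdict on failure.** The three-way list stands in the sample-size section. The Primary objective section says only when non-inferiority and superiority are accepted. One could read the list as naming possible conclusions, with the criterion for *inferior* left to the full protocol or analysis plan. It is true that no single sentence ties *inferior* to a lower limit at or below −15%; that follows from reading the two sections together. But the list is printed as complete, inferiority is the null of step 1, and the sentence justifying no alpha adjustment itself speaks of accepting inferiority. The article therefore states a rule rather than leaving one out.

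**No test changes.** The 19.2% is the planned type II error, and a reader given the interval could see that the result is inconclusive. This stands as a limit on the point. A reader might infer that the sample size is wrong or that the type I error of the non-inferiority test is inflated. The documents do not support that: 126 per arm reproduces, and the 5% level holds for the claim that it protects.

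**The figure is a worst case.** A reader might take one in five as a general rate. It is not. It belongs to the 65% assumption, which the article itself calls the most demanding in patients, and it falls to 4.7% at the top of the cited range. If Evodial brings the 15% to 20% improvement that the article cites for preheparinated membranes, the false label almost never occurs. This objection is accepted, and the size is stated with its condition.

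**A bare upper-limit rule would overlap.** An interval can lie wholly above −15% and wholly below 0; this occurs in 0.7% of trials at 85% vs 85%. The fix has to settle which label applies.

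**Conclusion.** The point holds. As written, the article turns failure to show non-inferiority into a conclusion of inferiority. That fault does not depend on any success rate. Its size does: with equal devices and 126 per arm, 19.2% at the design rate of 65%, falling to 4.7% at 85%. These figures assume no true difference, independent binomial outcomes, no dropout (as the article expects) and the Newcombe form of the Wilson interval. The normal approximation gives nearly the same value at 65% (19.7%). The fault lies in the reported conclusion, not in the design or the test.

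**What to change.** In Justification of sample size, replace the *inferior* outcome with *non-inferiority not demonstrated*, applied when the lower one-sided 95% limit is at or below −15%. This needs no new criterion.

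If the sponsor wants to keep an *inferior* verdict, allow it only when both conditions hold: non-inferiority is not demonstrated, and the upper one-sided 95% limit is below 0. The first condition makes the outcomes mutually exclusive, so an interval lying between −15% and 0 is reported as non-inferior. False *inferior* verdicts for an equal device are then held to about 5% at most.

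The cost is one sentence, repeated in the analysis plan if it uses the same list. Sample size, alpha, margin and conduct are untouched. With 245 patients recruited at submission of the article, the change affects only analysis and reporting; it should be made before the treatment comparison is seen.

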#### Primary objective

The success of hemodialysis is defined as the proportion of first treatment achieved without prematurely halting dialysis or having to change blood lines or dialyzer, owing to clotting or any additional saline flush because of clotting. The 95% one-tailed confidence interval of the test-reference difference will be constructed using the Wilson method [29], and non-inferiority then superiority accepted if its lower boundary is found to be greater than −15% then +15%. The consistency of responses across centers will be confirmed using the Breslow-Day test for homogeneity of odds ratios or logistic regression as appropriate. Though unexpected, the impact of maneuvers in the control arm (predilution or saline flushes, centre-specific) will be tested and, if necessary, taken into account as a nested factor in the analyses.

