Several protocols of heparin-free dialysis are currently being used in routine practice, which may include saline flushes delivered at frequent intervals, requiring close monitoring by dialysis staff, or predilution, where a continuous infusion of saline is run to the dialyzer; the former procedure being the most commonly used. Taking into account this heterogeneity and in order to increase the external validity of the study results, it was decided to allow both types of saline infusions, which reflect real-life situations; however, accompanied with guidelines relative to the volume and output of saline infusion, in order to minimize the heterogeneity within the control group. To the best of our knowledge, the HepZero study is the first international, multicenter, randomized, controlled study aimed at comparing two techniques of heparin-free dialysis, including its gold standard, in two parallel groups, in an open-label design. It is sufficiently powered to first evaluate the non-inferiority of Evodial (which may allow a decrease in dialysis staff workload during heparin-free dialysis sessions) then its potential superiority versus the standard care of saline infusions, and may therefore have major clinical implications for patient care.

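### The stated 80% power holds for non-inferiority only; under the plan's +15% superiority rule, power at the planned 65% control rate is about 5% to 23% for gains of 15 to 20 points

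*Protocol article*

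**What the plan says.** All of this is in the Protocol article.

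- **Justification of sample size, margins:** "The non-inferiority as well as superiority margins will be set to the same value of 15"%.
- **Justification of sample size, planning rate:** "In the hypothesis of a 65% success rate (the most patient-consuming) in the control arm", 126 patients per arm "will provide the trial with 80% power to first conclude to non-inferiority then to superiority, with a one-tailed 5% error rate".
- **Justification of sample size, background figures:** for current heparin-free methods "the success rate of hemodialysis ranges from 65% to 85"%, and recent work on preheparinated membranes is cited as improving these rates by 15% to 20%. No Evodial success rate or true difference is given at which the superiority step would have 80% power.
- **Efficacy analysis, Primary objective:** from a one-sided 95% Wilson interval for the difference, "non-inferiority then superiority accepted if its lower boundary is found to be greater than −15% then +15"%.
- **Discussion:** "It is sufficiently powered to first evaluate the non-inferiority of Evodial"; the same sentence goes on to extend this to superiority over saline infusion.

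The +15% boundary is not a slip in one place: the margin statement and the decision rule agree on it.

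**The concern.** One power figure is attached to two tests that ask for very different things. Non-inferiority asks the lower limit to clear −15% when the true difference is assumed to be zero, a distance of 15 points. Superiority asks it to clear +15% when the cited gain is 15% to 20%, a distance of 0 to 5 points if those are percentage points. One sample size cannot give 80% power for both.

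Superiority is the second step of the primary objective, and the plan fixes three possible conclusions: inferior, not inferior but not superior, or superior. A reader told that the trial had 80% power for superiority would take the middle conclusion as evidence against a benefit. If Evodial raised success from 65% to 80%, the trial would reach that middle conclusion about 95% of the time.

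**Working it through.** **Inputs** (Justification of sample size; Efficacy analysis, Primary objective): one-sided alpha 5%; 126 per arm; control success 65% for planning, 65% to 85% published; cited gain 15% to 20%; boundaries −15% and +15%; Wilson interval for the difference, taken here as the Newcombe score interval with a one-sided 95% limit. No dropout is expected (Patient populations).

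**1. Reproducing 126.** For non-inferiority with both arms at 65%:

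n = (z₀.₉₅ + z₀.₈₀)² × 2 × 0.65 × 0.35 / 0.15² = 125.03, rounded up to 126.

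This matches the plan exactly. At 126 per arm, power is 80.3% by the normal approximation and 80.8% by exact enumeration of both binomials. The calculation contains no superiority step.

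**2. Superiority by normal approximation, 65% vs 85%.**

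SE = √((0.65×0.35 + 0.85×0.15)/126) = √(0.355/126) = 0.0531

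(0.20 − 0.15)/0.0531 − 1.645 = −0.70, so power is about 24%.

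At 65% vs 80% the numerator is zero, so power equals alpha, 5%, whatever the sample size.

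**3. Exact enumeration, 126 per arm, lower limit above +15%.**

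| Control | Gain of 15 points | Gain of 20 points |
|---|---|---|
| 65% | 4.9% | 23.4% |
| 70% | 4.8% | 26.1% |
| 75% | 4.8% | 30.4% |
| 80% | 4.6% | 37.8% (Evodial 100%) |
| 85% | 3.3% (Evodial 100%) | not possible |

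**4. What 80% power would take.** At 65% control, a gain of 25 points gives 62.8%; 80% is reached at about 65% vs 92.2%, a gain of about 27 points. At 80% control it is not reached at any Evodial rate. For 65% vs 85%, the size per arm would be 0.355 × (z₀.₉₅ + z₀.₈₀)² / 0.05² = 877.9, so 878.

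**5. Relative reading of the gain.** At 65% control, 15% relative is 65 × 1.15 = 74.75% and 20% relative is 65 × 1.20 = 78%. Power against +15% is then 0.5% and 2.2%.

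**6. In observed counts.** With 82/126 control successes (65.1%), Evodial needs 112/126 (88.9%), an observed difference of 30/126 = 23.8 points. With 126/126 on Evodial, the rule is met only if control has at most 99/126 (78.6%).

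**7. Zero boundary, for comparison.** Power that the same limit exceeds 0 at 65% control: 85.4% for +15 points and 98.2% for +20 points; on the relative reading, 52% (65 vs 74.75) and 75% (65 vs 78).

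**The case against.** Several points on the other side are sound.

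- **The 80% is right for the gatekeeping step.** The sample size is correct for non-inferiority, and that conclusion is untouched. A reader might infer that the trial is too small for its purpose; the documents do not support that. The softer reading, that 80% was meant for non-inferiority only, explains the 126, but both the sample size section and the Discussion extend it to superiority.
- **About 5% at 65 vs 80 is designed behaviour.** The rule defines superiority as more than 15 points, so a true gain of exactly 15 lies on the null boundary and the 5% is type I error. What remains is that the boundary was put at the expected effect while 80% power was claimed. The error is conservative: it makes a superiority claim harder, not easier.
- **The criterion is not strictly unattainable at high control rates.** A reader might infer that it can never be met at 85%. The rule applies to the observed limit, which chance can carry past +15% (3.3% at 85 vs 100). What cannot exist there is a true gain above 15 points. At 80% vs 100% the rule is met 37.8% of the time.
- **The 5% to 23% range is conditional.** It holds at 65% control with gains in percentage points, not over all the plan's assumptions.
- **Relaxing the boundary now is risky.** The Trial status section reports 245 of 252 patients recruited (97%), the trial is open-label, the monitoring board sees efficacy data, and the sponsor has two seats on the committee that approves amendments. Lowering the bar from +15% to 0 would raise power at 65 vs 80 from 4.9% to 85.4% and could look data-driven. This objection stands and decides the order of the remedies.

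**Conclusion.** The power statement is wrong as written for the superiority step and correct for the non-inferiority step. With 126 per arm and the +15% rule, superiority has about 5% power for a 15-point gain and 23% for a 20-point gain at 65% control. The best case within the cited gains is about 38%, at 80% control with Evodial at 100%. At 65% control a relative reading of the gain lowers power to about 0.5% to 2%. No combination of the plan's control rates and cited gains comes near 80%.

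These figures assume the Newcombe form of the Wilson interval, 126 evaluable patients per arm and independent binomial outcomes; the normal approximation agrees closely at 65% control (5.0% and 24.1%). They do not show that the trial is undersized for non-inferiority or that a superiority finding is impossible.

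**What to change.** **Correct the power statements.** In the sample size section, limit the 80% to non-inferiority at 65% vs 65%. Then give the power of the +15% step with its assumptions, for example about 5% at 65 vs 80 and 23% at 65 vs 85, and say whether the 15% to 20% improvement is absolute or relative. Bring the Discussion sentence into line.

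**Name the claim for what it is.** Describe the second step as superiority by more than 15 points, and state that failing it is not evidence of no benefit.

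**Keep the pre-stated +15% rule by default.** Report the comparison with a zero boundary as a clearly labelled supplementary analysis.

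**Option.** Moving the superiority boundary to 0 would give about 85% power at 65 vs 80 (absolute gain). It should be done only by a dated amendment before database lock, with documentation that those deciding were blind to comparative data. Superior would then mean better than standard care, not better by more than 15 points.

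**Cost.** The corrections are wording only: no extra patients and no change to the decision rule. The option also needs no patients, but it carries the risk of seeming to lower the bar late in an open-label trial.

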### Efficacy analysis

#### Baseline comparability

The baseline comparability of groups will be checked, using the center as an adjustment factor. Should one or more factors show significant imbalance, the steering committee will assess the impact of the possible confounding factor(s) on further analyses and decide whether it is necessary to take it into account during the blind review of data. Adjustment will be performed using logistic regression.

#### Primary objective

The success of hemodialysis is defined as the proportion of first treatment achieved without prematurely halting dialysis or having to change blood lines or dialyzer, owing to clotting or any additional saline flush because of clotting. The 95% one-tailed confidence interval of the test-reference difference will be constructed using the Wilson method [29], and non-inferiority then superiority accepted if its lower boundary is found to be greater than −15% then +15%. The consistency of responses across centers will be confirmed using the Breslow-Day test for homogeneity of odds ratios or logistic regression as appropriate. Though unexpected, the impact of maneuvers in the control arm (predilution or saline flushes, centre-specific) will be tested and, if necessary, taken into account as a nested factor in the analyses.

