#### Secondary objectives

The treatment groups will be compared for efficacy (success rates in second and third treatments, achievement of the planned weight loss and UF volume) and safety using the Mantel-Haenszel test stratified on center or logistic regression as appropriate.

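### The primary Wilson interval names no centre stratification although randomisation and the secondary tests use it, and a weak odds-scale test cannot confirm that a risk difference is consistent across centres

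*Protocol article*

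**What the plan says.** All places are in the protocol article.

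- **Statistics:** "Patients will be assigned to treatment groups using block randomization stratified on centers".
- **Efficacy analysis, Primary objective:** "The 95% one-tailed confidence interval of the test-reference difference will be constructed using the Wilson method", with "non-inferiority then superiority accepted if its lower boundary is found to be greater than" −15%, then +15%. No centre term is named.
- **Same section, on centres:** "The consistency of responses across centers will be confirmed using the Breslow-Day test for homogeneity of odds ratios or logistic regression as appropriate". The effect of the control technique, which differs by centre, "will be tested and, if necessary, taken into account as a nested factor in the analyses".
- **Baseline comparability:** centre is an adjustment factor when the groups are compared at baseline. If an imbalance is judged important, "Adjustment will be performed using logistic regression".
- **Efficacy analysis, Secondary objectives:** the arms are compared "using the Mantel-Haenszel test stratified on center or logistic regression as appropriate".

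Centre therefore enters the randomisation, the baseline comparison and the secondary tests. In the primary analysis it enters only through a supporting check and a conditional adjustment.

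**The concern.** Three things do not fit together.

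1. **Design and analysis.** Randomisation within centres removes between-centre variation from the comparison of arms. An interval that ignores centre puts that variation back into the standard error. Each site uses its own usual control procedure (saline flushes or predilution), so some difference between centres is to be expected.
2. **Scale.** Non-inferiority and superiority are judged on a difference in proportions. Breslow-Day and logistic regression judge odds ratios. The conditional adjustments have the same difficulty: the article does not say how an adjusted odds ratio would be set against −15 or +15 points.
3. **Confirmation.** A non-significant homogeneity test with few patients per centre is weak evidence of anything, yet the text treats it as able to confirm consistency.

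At stake are a little precision in the primary test and, more importantly, a statement on centre consistency that the data could not support.

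**Working it through.** **Inputs from the article (Justification of sample size):** control success 65%, literature range 65% to 85%; margin 15 points; one-sided 5%; 80% power; 126 per arm; 10 centres with about 13 per arm each.

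**Assumption:** the between-centre spread is not given. Control rates are taken as evenly spaced over 65–85% (the literature range), with 45–85% and 35–95% as wider cases.

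**Step 1: the plan's own figure.** Without a centre term, n = (1.645 + 0.842)² × 2 × 0.65 × 0.35 / 0.15² = 125.03, rounded up to 126 per arm. Power at 126 is 80.3%. The stated size is reproduced for the non-inferiority step.

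**Step 2: precision, normal approximation.** Unstratified variance is 2p(1−p)/n with p the mean rate. Stratified variance is 2 × mean[p_c(1−p_c)]/n over centres. The two differ by 2 × (between-centre variance)/n.

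For 65–85%: p = 0.75 and the between-centre SD is 0.0638. The unstratified SE is √(2 × 0.1875/126) = 0.0546. The stratified SE is √(2 × (0.1875 − 0.0638²)/126) = 0.0540.

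| Control rates over centres | SE reduction | Non-inferiority power, unstratified → stratified |
|---|---|---|
| 65–85% | 1.1% | 86.8% → 87.2% |
| 45–85% | 3.6% | 81.2% → 82.8% |
| 35–95% | 8.4% | 82.4% → 86.0% |

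**Step 3: simulation with the planned type of interval.** The pooled Wilson-score (Newcombe) lower bound was compared with a centre-stratified risk difference. Error is taken at a true difference of −15 points and power at a true difference of 0.

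| Control rates | Error, pooled / stratified | Power, pooled / stratified |
|---|---|---|
| 65–85% | 5.2% / 5.2% | 87.4% / 87.4% |
| 35–95% | 4.2% / 5.0% | 82.9% / 86.2% |

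A separate run with 13 per arm in every centre (130 per arm) agrees: 88.3% against 88.0% power for 65–85%, and 84.6% against 87.1% for 35–95%.

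**Step 4: scale.** A difference of −15 points at 65% is an odds ratio of (0.50/0.50)/(0.65/0.35) = 0.538. The same odds ratio gives −13.2 points at 75% and −9.7 points at 85%. Conversely, a constant −15 points gives odds ratios of 0.54, 0.50 and 0.41 at 65%, 75% and 85%. Equal odds ratios are not equal risk differences unless there is no effect.

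At this centre size the mismatch is hard to see. Breslow-Day at the 5% level rejects in 4.7% to 5.6% of trials when the risk difference is constant at −15, 0 or +10 points over 65–85%.

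**Step 5: power of the homogeneity test.** Ten centres, 13 per arm each, control rate 65%, 3,000 simulated trials. The article states no level for this test, so two are shown.

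| True centre differences | Rejects at 5% | Rejects at 10% |
|---|---|---|
| Half 0, half −20 points | 17% | 28% |
| Half +15, half −15 points | 40% | 54% |

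In the first case half the centres lie beyond the −15-point margin, yet at the 5% level about five trials in six (1 − 0.17 = 0.83) would pass the check.

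**The case against.** **The interval may not be unstratified.** The article names the Wilson method and is silent on centre. A stratified score interval in the full protocol or analysis plan is not excluded. This stands, so the point concerns what the article fixes and should be settled in the wording.

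**Centre is not ignored.** The article tests the centre-specific control technique and would add it as a nested factor if needed, and it allows logistic regression as well as Breslow-Day. This also stands. However, these steps are conditional and, where logistic, on the odds scale. The article does not say how they would lead to a lower bound comparable with the 15-point boundaries.

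**The primary test may look materially conservative.** A reader might infer this from a pooled Wald interval: with a between-centre SD of 10 points its error is about 4.5%. The plan names Wilson. With the Wilson-score bound and the same spread, error is 5.1% against 5.0% stratified, and power is 81.6% against 82.1%. Clear conservatism appears only at very wide spreads that the article does not give.

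**The trial may look short of non-inferiority power.** The documents do not support this. The size rests on the most demanding control rate in the range and on no true difference, while an improvement of 15% to 20% is cited.

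**The homogeneity check does not drive the decision.** This is true, and it limits the consequence of the scale mismatch. It does not rescue the claim that the check confirms consistency.

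**Conclusion.** The point holds as a minor improvement. The primary interval, as written, names no centre stratification, unlike the randomisation and the secondary tests. The consistency check is on a different scale from the boundaries, and with about 13 patients per arm per centre it cannot confirm consistency.

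The documents do not support calling the unstratified Wilson interval invalid. It shows no material inflation of type I error, and when it errs it errs on the conservative side. The precision gain from stratifying is negligible over 65–85% and about 1 to 3 points of power over 45–85% to 35–95%. Those spreads are assumptions, with evenly spaced centre rates and equal centre sizes. The weakness of the homogeneity test depends far less on them, because it follows mainly from the number of patients per centre.

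**What to change.** - **Primary:** estimate the risk difference stratified by centre with Mantel-Haenszel weights. Compare a stratified Newcombe/Wilson one-sided 95% lower bound with the same boundaries. With balanced allocation inside centres the point estimate hardly moves; only the width of the interval changes.
- **Sensitivity:** keep the unstratified Wilson interval.
- **Consistency:** show the risk difference with its interval for each centre, for example in a forest plot, and describe the pattern. Drop the statement that consistency is confirmed. Breslow-Day may stay as a supporting result.
- **Conditional adjustments:** if a baseline factor or the control technique is adjusted for, state how the result is returned to the risk-difference scale.

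The cost is a few sentences and a few lines of code. No patients are needed and 126 per arm is unaffected. The article reports 245 patients already recruited, so the wording should be fixed and dated before any comparison of outcomes by arm.
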